### 14.1 A description of the statistical methods to be employed, including timing of any planned interim analysis(es).

All serum antibody concentrations will be log transformed for statistical analysis as geometric mean concentrations (GMC). Where protective thresholds are well established, the proportions at or above the assay cut off – anti-diphtheria (0.1 IU/ml)\*, anti-tetanus (0.1 IU/ml) anti-Hib (PRP) (0.15 µg/ml) and hepatitis B surface antibody (10mIU/ml) – will be compared by vaccine group. Antibody to polio serotypes 1, 2 and 3 will be measured by microneutralisation assay and the lowest dilution tested at 1:8. Statistical analysis will include both comparisons of GMC (with 95% confidence intervals) as a continuous variable (t test) and categorical analysis of relevant Ab. Thresholds (chi square). Analysis will be performed with the assistance of the NHMRC Clinical Trials Centre, independent of the testing laboratory. *Note: \* this threshold is significantly above the known protective level of 0.01 IU/ml but is the lower limit of assay detection.*

The primary analysis will be a comparison in the susceptibility rate (no measurable PRN nor PT) between the two groups at week 10 (or last post-baseline observation carried forward) using a chi-square test. The applicability of more sophisticated analysis approaches that adjust for covariates (e.g. logistic regression) and model the repeated assessments of susceptibility over time Week 6, Week 10, Month 6, Month 8 will be investigated.

The other antibody threshold data collected at Month 8 will be analysed using same approaches as those outlined above for the Week 10 susceptibility data.

The log-transformed antibody concentrations will be analysed using a linear model with treatment group, site and maternal dTpa vaccine status as factors. The applicability of repeated measures analysis methods (e.g. mixed-model) will also be explored for the concentration data.

The analysis of safety data will be primarily descriptive in nature.

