| Subjects   |                                           | 220                                                                                                                                                                                                                                                                                     | 220                                                                                                                                                                                                                                                               |
| Visit no.  |                                           |                                                                                                                                                                                                                                                                                         |                                                                                                                                                                                                                                                                   |
| 1   | Birth
(Birth to <120 hours old) | Maternal blood sample*
Pertussis antibodies

Vaccine administration
HepB 1 aP 1
Observations
Reactogenicity 1
Parental vaccine
dTpa (Boostrix) booster                                             | Maternal blood sample*
Pertussis antibodies

Vaccine administration
HepB 1
Observations
Reactogenicity
Parental vaccine
dTpa (Boostrix) booster                                                    |
| 2   | 6 weeks
(42 56 days)            | Blood sample (6 weeks post dose 1)
Pertussis antibodies
Vaccine administration
D 1 T 1 Pa 2 -HepB 2 -IPV 1 -PRP-T 1
Rotavirus vaccine
Synflorix
Observations
Reactogenicity | Blood sample
Pertussis antibodies
Vaccine administration
D 1 T 1 Pa 1 -HepB 2 -IPV 1 -PRP-T 1
Rotavirus vaccine
Synflorix
Observations
Reactogenicity |

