|          |                                   |                                                                                                                                                                                                                                                                                                 |                                                                                                                                                                                                                                                                                                 |
|----------|-----------------------------------|-------------------------------------------------------------------------------------------------------------------------------------------------------------------------------------------------------------------------------------------------------------------------------------------------|-------------------------------------------------------------------------------------------------------------------------------------------------------------------------------------------------------------------------------------------------------------------------------------------------|
| 3 | 10 weeks                   | Blood sample (28-35 days post dose 2)
Pertussis antibodies
Cell mediated immunity (subset only)                                                                                                                                                                                    | Blood sample (28-35 days post dose 1)
Pertussis antibodies
Cell mediated immunity (subset only)                                                                                                                                                                                    |

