## 11 Assessment of Efficacy

### 11.1 Specification of the efficacy parameters.

Blood samples will be taken as follows: maternal blood at birth, infant blood at 6 weeks, 10 weeks, 6 and 8 months. We believe that each of these blood samplings is important in the evaluation of antibody kinetics and comparison of the two groups in terms of presumed disease protection.

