### **14.5 Procedure for accounting for missing, unused and spurious data.**

From an analysis perspective, a 'drop-out' will be any subject who did not attend the concluding visit. A participant, who returns for the concluding visit in the protocol, even if not all prior visits were attended, is deemed to have completed the study.

Methods for imputing missing values (e.g. last post-baseline observation carried forward) or analysis models that accommodate missing data (e.g. repeated measures mixed-models) will be employed where necessary to ensure as many subjects as possible from the Full Analysis Set contribute to the efficacy analyses.

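### Carrying the 6-week sample forward to week 10 mixes a one-dose-versus-none contrast into the primary two-versus-one comparison and can bias it in either direction

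*Protocol*

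**What the plan says.** Section 14.1 makes the primary analysis a comparison of susceptibility (no measurable antibody to PT or PRN) between the two vaccine groups "at week 10 (or last post-baseline observation carried forward) using a chi-square test". Section 14.5 repeats the device as an example: "Methods for imputing missing values (e.g. last post-baseline observation carried forward", with mixed models for repeated measures named as an alternative.

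Section 11.1 lists the blood samples as "maternal blood at birth, infant blood at 6 weeks, 10 weeks, 6 and 8 months". Table 3 in Section 8.3.2 agrees: the birth sample is the mother's, and the infant is bled at visits 2, 3, 5 and 6. Section 14.1 itself counts the 6-week value as an outcome assessment when it proposes to "model the repeated assessments of susceptibility over time Week 6, Week 10, Month 6, Month 8".

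In the schedule and groups table (Table 2, Section 8.1.2), the visit-2 entry for the birth group reads "6 weeks post dose 1) Pertussis antibodies Vaccine administration", so the blood sample comes first and the label counts one dose. The control entry has the same order, with the first pertussis dose given at that visit. The week-10 sample is "28-35 days post dose 2" in the birth group and the same interval after dose 1 in controls.

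The opening of Section 14 and Section 14.6 define the efficacy set as everyone randomised.

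**The concern.** A carried-forward value should be a tolerable stand-in for the missing one. Here a vaccine dose lies between the two samples in both groups. A control's 6-week value can reflect only antibody from the mother, which Section 2.2.3 says falls quickly after birth. Such a control may be scored protected at week 10 on antibody that has since waned, or susceptible despite an unmeasured response to the first dose. A birth-group infant's value shows the response to one dose, not two.

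At stake is the primary estimate. The contrast differs by design between the two time points, so the bias does not depend on why samples are missing. The trial is also open-label (Section 5.1), so the share missing may differ between groups, which would add to the problem. The chi-square test treats carried values as if they had been observed at week 10.

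**Working it through.** **Which value can be carried.** The infant samples are at 6 weeks, 10 weeks, 6 months and 8 months, so only the 6-week value precedes week 10. The protocol does not define baseline. If week 6 were baseline, there would be nothing to carry and the rule would be empty; Section 14.1's list of repeated assessments points the other way.

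| Sample | Birth group, prior pertussis doses | Control, prior pertussis doses |
|---|---|---|
| 6 weeks | 1 | 0 |
| 10 weeks | 2 | 1 |

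That the 6-week blood is taken before the injection is inferred from the visit order and the dose label; no sentence states it. It matters little, because a sample taken at the same visit could not show a response to that visit's dose.

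**The plan's own figure.** Inputs from Section 14.2.1: 12-point reduction, 80% power, two-sided alpha 0.05, 10% drop-out, and 65-75% of controls with detectable antibody, read as 25-35% susceptible. At the midpoint, 30% versus 18%, with mean rate 0.24:

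n = [1.960 × √(2 × 0.24 × 0.76) + 0.842 × √(0.30 × 0.70 + 0.18 × 0.82)]² / 0.12² = 198 per group, and 198 / 0.9 = 220.

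This matches the 220 per vaccine group in Table 2.

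**Bias.** Let m be the share of infants whose week-10 result is carried forward, equal in both groups. Each group's expected rate is (1 − m) × week-10 rate + m × week-6 rate, so

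bias = m × (week-6 gap − week-10 gap), where gap = control rate minus birth-group rate.

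Assumptions, none of which the protocol gives directly:
- m = 5-10%. The protocol's only loss figure is the 10% drop-out allowance.
- Control susceptibility at week 6 of 25-35%, taking Section 14.2.1's pre-immunisation range as the 6-week value.
- Birth-group susceptibility at week 6 anywhere from 0 to the control rate, so the week-6 gap is 0 to 35 points.
- A true week-10 gap of 12 points.

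| Week-6 gap (points) | Bias, m = 5% | Bias, m = 10% | Estimate, m = 10% |
|---|---|---|---|
| 0 | -0.6 | -1.2 | 10.8 |
| 12 | 0 | 0 | 12.0 |
| 25 | +0.65 | +1.3 | 13.3 |
| 35 | +1.15 | +2.3 | 14.3 |

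For example, 0.10 × (0 − 12) = -1.2 and 0.10 × (35 − 12) = +2.3.

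**Power.** At 30% versus 18% with 220 per group, power with complete week-10 data is 0.841. With 10% carried forward and 30% susceptible in both groups at week 6, it is 0.750. Analysing only the 198 observed per group gives 0.801, so in this case carrying forward is worse than leaving those infants out. With 198 per group, power at control rates of 25%, 30% and 35% is 0.864, 0.801 and 0.751.

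**False positives.** Suppose 30% are susceptible in both groups at week 10, but 30% versus 10% at week 6. The spurious difference is m × 20 points: 1 point at m = 5% and 2 points at m = 10%. The rejection rate with 220 per group is about 5.6% and 7.5%, against a nominal 5%.

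**The case against.** The strongest reply is that the rule touches few infants and that its effect is modest and of unknown sign. Much of this stands.

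- A reader might infer that the primary test becomes a one-versus-none comparison. It does not. Only infants with a 6-week but no 10-week result are affected; the rest contribute the intended contrast.
- A reader might expect carry-forward always to favour the birth dose, perhaps by up to 4 points. That would take something like 20% carried forward and a week-6 gap 20 points wider than the week-10 gap. No missing rate of that size appears in the protocol. A 32-point gap would need birth-group susceptibility of -7%, -2% or 3% when controls are at 25%, 30% or 35%. If the groups are alike at week 6, the bias is against the vaccine.
- A reader might infer general inflation of type I error. If the birth dose has no effect at either visit and missingness is unrelated to group, carry-forward adds no bias. Inflation needs an early benefit that is gone by week 10.
- Section 14.1 also says "The other antibody threshold data collected at Month 8 will be analysed using same approaches", which might suggest that the Month-8 results are distorted too. Those concomitant antigens are measured once, so nothing can be carried and no result changes.

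It can also be said that Section 14.5 gives carry-forward only as an example, that Section 14.1 foresees modelling, and that imputation details belong in a statistical analysis plan. But Section 14.1 writes carry-forward into the primary analysis itself and leaves the models to be investigated. This is a stated rule, not an omitted detail.

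**Conclusion.** The point holds for the primary week-10 analysis. Infants with a 6-week but no 10-week result enter with one dose versus none, so the estimate is a mixture of two contrasts and can be biased in either direction even under missing completely at random. Under the assumptions above, the bias is about -1.2 to +2.3 points on a 12-point target. That range depends on the assumed 5-10% carried forward and on reading the 65-75% detectable-antibody range as the controls' 6-week value; the structural fault depends on neither.

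The rule also fails in its apparent purpose. Infants with neither sample still have no value, so it does not deliver an analysis of everyone randomised. Nor is it needed for power at the planning midpoint, since the sample size already allows for 10% loss.

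**What to change.** Remove carry-forward from the primary analysis in Section 14.1, and state that it is not used for week 10 under Section 14.5. Whether the general example in Section 14.5 also goes is secondary.

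Make the primary analysis a comparison of observed week-10 results by randomised group. As a supportive analysis, impute week-10 PT and PRN by multiple imputation from group, maternal stratum, site, maternal IgG and the infant's other samples. Those samples carry indirect information about the missing value, which a model can use without equating the 6-week result with the 10-week one. The order of the two analyses is a matter of choice, provided it is fixed beforehand.

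Align the opening of Section 14 and Section 14.6, which promise efficacy analyses on everyone randomised, with a primary analysis limited to infants who have a week-10 result.

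The cost is a few sentences and routine programming. The primary n falls by the infants without a week-10 sample. The 10% allowance in Section 14.2.1 covers this: 198 per group gives about 80% power at 30% versus 18%. At 35% versus 23% power is about 75%, but there even complete data on 220 per group give only 0.794.

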### 5.2 Stratification

This will be by maternal immunisation status / past history of pertussis infection before randomization in two groups:

**Stratum A** – maternal dTpa vaccine or history of maternal pertussis infection within last 5 years.

**Stratum B** – no previous maternal dTpa vaccine or dTpa vaccine > 5 years pre-delivery and no history of maternal pertussis infection during last five years.

A maternal history of Pertussis infection will be accepted as positive if the participant's mother reports that the diagnosis was made by blood test or throat swab and confirmation of diagnosis via blood test or throat swab is received by her healthcare provider.

NOTE: If a mother receives dTpa vaccine after delivery of child but before enrolment of infant then infant should be stratified into stratum B.

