### 5.3 Randomisation

Once written informed consent has been provided and eligibility has been confirmed, the participant will be issued with a unique participant number. The participant number will be used to identify the participant for the duration of the study. Neonates will be randomly assigned, in a 1:1 ratio to one of two groups (Table 2):

**Birth group** (early vaccination) Pa vaccine at birth, 6 weeks, 4 months and 6 months.

**Control group** (standard vaccination) usual vaccinations at 6 weeks, 4 months and 6 months.

[figure not shown]

Participants will be randomized using the central randomisation service at the NMHRC Clinical Trial Centre, Sydney, by automated interactive voice response system (IVRS) (available 24hrs). Investigators and study research staff will follow the voice prompts on the IVRS and complete the randomisation worksheet. Participants will be allocated to either the Pa vaccine at birth or No Pa vaccine given at birth groups via the IVRS.

Before randomisation, stratification into either the 'maternal dTpa vaccine prior to birth within 5 years' group / history of maternal pertussis infection < 5years **or** no maternal dTpa

vaccine < 5years / no history of maternal pertussis infection < 5years will be conducted according to maternal verbal report.

Subsequently attempts will be made to confirm maternal verbal report of receipt of dTpa vaccine or history of laboratory confirmed maternal infection by obtaining verification from the maternal healthcare provider. If no confirmation of mother having received dTpa vaccine within last 5 years (prior to enrolment) or history of laboratory confirmed maternal infection with pertussis is obtained, the mother/infant will be re-allocated to the no maternal dTpa vaccine group for the purpose of secondary analysis only.

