### 14.2 The number of subjects planned to be enrolled.

#### 14.2.1 Antibody measures:

Lack of any measurable antibody to both PT and PRN is the best available indicator of susceptibility to severe pertussis. Accordingly, we have based sample size calculations on reduction in the proportion of susceptible infants as early as possible. If superiority of birth pertussis vaccine is defined as a reduction of 12% or more in the proportion of subjects

lacking antibody (no measurable PRN or PT) compared with controls at 10 weeks old, a sample size of 220 in each maternal arm will have 80% power to detect a reduction of this magnitude at a two-sided alpha level of 0.05. This is not altered by a differing prevalence of detectable pre-immunisation antibody among controls over the range of 65% to 75%. (Sample Power V2 [www.spss.com](http://www.spss.com)) This study will recruit 110 participants in each of the 4 arms, a total of 440 participants allowing for a 10% drop out rate.

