### **14.3 The level of significance to be used.**

Hypothesis tests and confidence intervals will be two-sided with alpha set to 5%.

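### The primary chi-square ignores the maternal stratum used in randomisation; a stratified test is a free improvement that gains 0 to about 6 points of power

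*Protocol*

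**What the plan says.** Section 5.2 of the protocol sets up stratified randomisation: "This will be by maternal immunisation status / past history of pertussis infection before randomization in two groups". Stratum A has maternal dTpa or pertussis infection in the last five years; stratum B has neither. Under section 5.3, "Neonates will be randomly assigned, in a 1:1 ratio to one of two groups", with the stratum taken from the mother's verbal report before randomisation. Infants whose maternal history cannot be confirmed are moved to the other group for secondary analysis only, so the stratum as randomised is kept. Section 14.2.1 plans 110 infants in each of four stratum-by-treatment cells.

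The primary analysis in section 14.1 compares susceptibility (no measurable PRN or PT antibody) "between the two groups at week 10 (or last post-baseline observation carried forward) using a chi-square test". The stratum plays no part in it. The test and the only mention of adjustment for this endpoint stand side by side: "using a chi-square test. The applicability of more sophisticated analysis approaches that adjust for covariates (e.g. logistic regression". The adjusted approaches are only to be investigated, and no covariate is named. Month-8 threshold data follow the same approaches. The linear model for log concentrations, also in section 14.1, has treatment group, site and maternal dTpa status as factors.

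**The concern.** The endpoint is the absence of measurable pertussis IgG, and the stratification factor is the mother's recent pertussis vaccination or infection. Passively transferred maternal antibody could make the two strata differ in susceptibility, although section 2.2.3 says that it declines rapidly after birth.

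If the strata do differ, stratified randomisation balances them between the arms. The plain chi-square nevertheless counts the between-stratum variation as noise. Its standard error is then too large for the design, its true type I error falls below 5%, and it has less power than a test that uses the stratum. Section 14.1 is also uneven: maternal status enters the concentration model but not the primary test. What is at stake is efficiency in the main comparison.

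**Working it through.** **Inputs from the protocol**
- Two-sided 5% level (section 14.3: "Hypothesis tests and confidence intervals will be two-sided with alpha set to 5"%).
- Sample size: "a sample size of 220 in each maternal arm will have 80% power to detect a reduction of this magnitude" (section 14.2.1). I read this as 220 per treatment group, as in Table 2, since 440 infants are planned in all.
- Drop-out 10%, so 110 × 0.9 = 99 evaluable per cell and 198 per group.
- Effect: "a reduction of 12% or more in the proportion of subjects" lacking antibody, read as 12 percentage points. A relative 12% would need roughly 2,000 to 3,100 per group.
- Control susceptibility 25% to 35%, the complement of the 65% to 75% antibody prevalence in section 14.2.1.

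**Assumptions.** The protocol does not give the gap in control susceptibility between strata. I use 0 to 40 percentage points, with equal strata (from 110 in each of four cells).

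**Step 1: reproduce the planned size.** For an unstratified two-proportion test,

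n = [1.96·√(2p̄(1−p̄)) + 0.8416·√(p₁(1−p₁) + p₂(1−p₂))]² / 0.12².

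At 30% vs 18%, p̄ = 0.24 and n = [1.96·√0.3648 + 0.8416·√0.3576]² / 0.0144 = 197.7, so 198 per group. Then 198/0.9 = 220, the stated figure. At 25% vs 13% n is 167; at 35% vs 23% it is 224. The planned size therefore rests on an unstratified test.

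**Step 2: true size of the chi-square.** With equal strata and 1:1 allocation within each, the chi-square uses the variance p̄(1−p̄), but the design leaves only the within-stratum part. The ratio of the two is

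r = 1 − (gap/2)² / [p̄(1−p̄)], and true size = 2·[1 − Φ(1.96/√r)].

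At a mean rate of 30%, p̄(1−p̄) = 0.21:
- 10-point gap: r = 1 − 0.0025/0.21 = 0.988, size 4.9%
- 20-point gap: r = 1 − 0.01/0.21 = 0.952, size 4.5%
- 30-point gap: r = 1 − 0.0225/0.21 = 0.893, size 3.8%
- 40-point gap: r = 1 − 0.04/0.21 = 0.810, size 2.9%

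Mean rates of 25% and 35% give 3.7% and 3.9% at a 30-point gap, and 2.7% and 3.1% at 40. Simulation agrees to about 0.1 point and puts the Cochran-Mantel-Haenszel (CMH) test at about 5% throughout.

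**Step 3: power, by simulation.** 198 evaluable per group, at least 200,000 replicates per setting, average reduction 12 points. Entries are chi-square / CMH, in %. The first three columns assume a common odds ratio across strata. The last assumes a 12-point reduction in each stratum.

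| Gap (points) | Mean 25%, common OR | Mean 30%, common OR | Mean 35%, common OR | Mean 35%, 12 points in each |
|---|---|---|---|---|
| 0 | 87.0 / 87.0 | 80.3 / 80.4 | 75.1 / 75.2 | 75.2 / 75.2 |
| 10 | 87.1 / 87.2 | 80.4 / 80.7 | 75.3 / 75.7 | 75.4 / 75.8 |
| 20 | 87.5 / 88.2 | 80.8 / 81.8 | 75.6 / 76.8 | 75.7 / 77.3 |
| 30 | 88.0 / 89.7 | 81.4 / 83.8 | 76.3 / 79.0 | 76.5 / 80.1 |
| 40 | 89.0 / 91.8 | 82.4 / 86.5 | 77.0 / 81.7 | 77.7 / 84.1 |

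The gain is 0 to 0.1 points at no gap, 0.1 to 0.4 at 10, 0.7 to 1.6 at 20, 1.7 to 3.6 at 30 and 2.8 to 6.4 at 40. With all 220 per group evaluable and a common odds ratio, the gains are slightly smaller: 1.5 to 2.3 points at a 30-point gap and 2.4 to 4.0 at 40. With strata split 20:80 and 220 per group, gaps of 20 to 30 points gave gains of about 0.5 to 1.3.

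**The case against.** The case for leaving the test alone is substantial.

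- **Is the factor prognostic?** A reader might infer that maternal vaccination or infection directly determines infant antibody at week 10. The protocol does not say so. Section 2.4.2 calls the effect of maternal antibody on vaccine responses uncertain, hypothesis 3 in section 3.2 expects no significant difference by maternal vaccination, and section 4.2 makes it a secondary question. By week 10 controls have had one Pa dose and the birth group two, so any gap at birth may have narrowed. This stands, and is why the range starts at zero.
- **Is planned power lost?** A reader might infer that the plan throws away power that the sample size relies on. Step 1 shows otherwise. Chi-square power in fact rises slightly as the strata diverge (75.1% to 77.0% in the third column). The loss is only relative to a better test. The figures near 75% come from the 35% control rate with drop-out, not from ignoring the stratum.
- **Is the test invalid or the estimate biased?** Neither. The chi-square errs on the conservative side, and with 1:1 allocation within strata the crude risk difference is unbiased.
- **Is the adjusted model a choice made after seeing the data?** The document does not support that. The primary test is fixed, and the form of a supportive logistic model may properly sit in a statistical analysis plan that is not shown.

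None of this argues for preferring the unstratified test. With no gap between strata, the two tests have the same power to within 0.1 point.

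**Conclusion.** The point holds as one of efficiency and consistency. The protocol fixes a primary test that ignores its own stratification factor, while adjusting the concentration model for maternal dTpa status. The test is valid and the planned size does not depend on stratifying.

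If the strata differ in susceptibility by up to 20 points, the loss is at most about 1.5 points of power. At 30 points it is about 2 to 4. At 40 it is about 4 to 6 for mean control rates of 30% to 35%, and about 2.5 to 3 at 25%, where power is already near 90%. True size drops to about 4% at a 30-point gap and about 3% at 40. These figures rest on assumed gaps, equal strata and a 12-point average reduction.

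This is a free improvement: it has an upside if the factor matters and essentially no downside if it does not.

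**What to change.** In section 14.1, make the primary analysis of week-10 susceptibility a Cochran-Mantel-Haenszel test stratified by the maternal stratum as randomised, reported with a stratum-weighted risk difference and its 95% confidence interval. Keep the plain chi-square as a sensitivity analysis. Apply the same approach to the Month-8 threshold endpoints, which section 14.1 already ties to the primary method. State that the stratum is the one used at randomisation, not the later confirmed maternal status, which section 5.3 reserves for secondary analysis.

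The cost is a sentence or two. The stratum is determined before randomisation for every infant, so no new data and no change to the sample size are needed.

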#### *2.4.2 Influence of maternal antibody:*

The effect of pre-existing maternal pertussis Abs, particularly higher levels resulting from maternal immunization, on responses to Pa vaccines at birth or subsequently is uncertain. Our pilot data suggest that two doses of Pa vaccine (at birth and 1-2 months old) are immunogenic in the presence of detectable maternal antibody, but did not include immunised mothers. Since 2007, NSW Health has required that all healthcare workers with patient contact be given dTpa booster vaccination and non-mandatory guidelines are in place in other jurisdictions. As healthcare workers participate more commonly in vaccine trials, this should facilitate recruitment to a study arm with mothers immunised with dTpa. Irrespective of the results of maternal immunisation studies, the question of persistence of adequate antibody in subsequent pregnancies remains.

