### 4.2 Secondary

1. To determine whether maternal receipt of adult-formulated acellular pertussis vaccine (dTpa) within the previous 5 years influences infant Ab or CMI responses.
2. To evaluate interactions with vaccine antigens given concurrently at birth (hepatitis B) or later
3. To evaluate adverse clinical or immunological effects from early use of Pa vaccine.

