#### *11.1.1 Antibodies to pertussis:*

IgG to PT, pertactin and FHA will be measured by ELISA in maternal and infant serum samples at GSK Biologicals, Belgium, using a validated assay.

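### The stated antibody concentration model does not estimate whether maternal status changes the birth-dose effect, and it leaves the measured maternal pertussis IgG unused

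*Protocol*

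**What the plan says.** Section 14.1 fixes the model for log concentrations: "The log-transformed antibody concentrations will be analysed using a linear model with treatment group, site and maternal dTpa vaccine status as factors". It adds: "The applicability of repeated measures analysis methods (e.g. mixed-model) will also be explored for the concentration data". No terms are named for that further model. Covariate adjustment is left open only for the susceptibility endpoint.

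Four other places bear on this:

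- Section 2.4.2, within the rationale and key questions for the design, says of maternal antibody that the "effect of pre-existing maternal pertussis Abs, particularly higher levels resulting from maternal immunization, on responses to Pa vaccines at birth or subsequently is uncertain". It adds that the pilot included no immunised mothers.
- Section 5.2 stratifies randomisation on maternal dTpa **or** maternal pertussis infection in the last 5 years. Section 5.3 says this is done on verbal report, and that unconfirmed cases are moved to the no-dTpa group for secondary analysis only.
- Section 11.1.1 says "IgG to PT, pertactin and FHA will be measured by ELISA in maternal and infant serum samples". Table 2 places the maternal sample at the birth visit.
- Section 4.2, objective 1, asks whether maternal dTpa within 5 years "influences infant Ab or CMI responses". Hypothesis 3 in section 3.2 compares infants of vaccinated and unvaccinated mothers.

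**The concern.** Section 2.4.2 asks whether maternal antibody changes the infant's response to a birth dose. That is a contrast of contrasts: birth versus control in one maternal stratum, minus the same difference in the other. A model with group, site and maternal status as separate factors takes that difference to be zero. If the birth dose works well in one stratum and poorly in the other, the model returns roughly the average and does not show the split.

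The maternal main effect is no substitute. At the 6-week sample controls have had no earlier Pa dose, so a maternal difference among them is most simply passive antibody. In the birth group the same difference combines passive antibody with any blunting of the response, and these can work in opposite directions. Pooled over groups, they could partly cancel.

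Two smaller points concern the same sentence. The model factor is narrower than the stratification factor: an infant whose mother had infection but no dTpa is in Stratum A, yet on a literal reading counts as dTpa-negative in the model. And maternal IgG is the only antibody baseline available, because no infant blood is drawn before visit 2.

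**Working it through.** **Inputs.** Sections 14.2.1 and 14.3: 110 infants in each of 4 arms, 440 in total, 10% dropout, two-sided alpha 0.05, 80% power, a 12-point reduction, and 65 to 75% of controls with detectable antibody (read as 25 to 35% susceptible). The documents give neither an SD for log pertussis IgG nor a correlation between maternal and infant IgG. Results are therefore in SD units, over an assumed range of correlation.

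**The plan's own figure.** For 30% versus 18% susceptible, mean proportion 0.24:

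n = [1.960 × √(2 × 0.24 × 0.76) + 0.842 × √(0.30 × 0.70 + 0.18 × 0.82)]² / 0.12² = 198 per vaccine group, and 198 / 0.9 = 220.

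This reproduces 220 per group. It leaves 198 evaluable per vaccine group, or 110 × 0.9 = 99 per cell of the group-by-stratum table if the cells are equal.

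**Detectable effects** (z sum 1.960 + 0.842 = 2.802):

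| Contrast | SE in SD units | Detectable at 80% power |
|---|---|---|
| Overall birth versus control | √(2/198) = 0.101 | 0.28 SD |
| Birth versus control in one stratum | √(2/99) = 0.142 | 0.40 SD |
| Group × stratum interaction | √(4/99) = 0.201 | 0.56 SD |

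Power for an interaction of size d is Φ(d / 0.201 − 1.960): about 29% at d = 0.28 and about 70% at d = 0.5.

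**Unequal strata.** With a and b evaluable infants per vaccine group in the two strata (a + b = 198), the SE is √(2/a + 2/b). If Stratum A held a quarter of infants (a = 49.5, b = 148.5), the detectable interaction would rise to 2.802 × 0.232 = 0.65 SD.

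**Precision from maternal IgG.** Adjustment multiplies residual variance by 1 − r², where r is the partial correlation given the factors already in the model.

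| Assumed r | Variance removed | SE multiplied by |
|---|---|---|
| 0.3 | 9% | 0.95 |
| 0.5 | 25% | 0.87 |
| 0.6 | 36% | 0.80 |

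Section 2.2.3 says passively transferred antibody falls quickly after birth, so the gain is probably smaller at 6 and 8 months than at 6 and 10 weeks.

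**The case against.** The strongest reply is that the formal questions are already covered. Objective 1 and hypothesis 3 ask whether infants of dTpa-vaccinated mothers differ from the others. That is a main effect, and the stated model contains it. Effect modification appears only in the rationale. This stands: no stated objective or hypothesis is left without an analysis.

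Second, interaction terms and covariates often belong in the SAP, which is not shown, and section 14.1 does not say that interactions are excluded. This stands in part. The protocol does name a specific set of factors, and neither of its open-ended sentences mentions maternal antibody or effect modification. Amending that sentence is more than filling in deferred detail.

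Third, maternal IgG lies on the pathway from maternal dTpa to infant antibody. Putting it in the model that answers hypothesis 3 would adjust away part of the effect being asked about. This is correct, and it is why the fix uses separate models.

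Fourth, dTpa status may be shorthand for the stratum, since section 5.3 applies the no-dTpa label even where it is a reported infection that could not be confirmed. That is possible, but the wording should then say so.

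A reader might also infer that every GMC-ratio interval is wider than it need be. The documents do not support that: maternal serum is assayed only for pertussis antigens, so no such covariate exists for diphtheria, tetanus, Hib, hepatitis B or pneumococcal antibody. Section 14.1 also lists a t test for the same GMCs. With 1:1 randomisation that test is valid, so naming one main analysis is only a matter of tidiness.

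**Conclusion.** This is a nearly free improvement to a secondary analysis. As written, the concentration model does not estimate whether maternal status or maternal antibody modifies the birth-dose effect, its maternal factor does not match the stratification factor, and a measured baseline goes unused.

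It would be tempting to conclude that the four-arm design cannot answer the maternal-antibody question. It can: stratified randomisation and the maternal assay supply what is needed, and only the stated model omits it. The primary comparison of susceptibility at week 10 is untouched.

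The 0.56 SD figure rests on four equal cells of 99 and a normal approximation. It shows that the interaction will be imprecise, so a non-significant result should not be read as no modification. The 9 to 36% range depends wholly on an assumed partial correlation, so the precision actually lost cannot be computed from the documents.

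**What to change.** Replace the one model sentence in section 14.1 with the following.

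- **(a) Birth versus control, infant PT, PRN and FHA IgG:** fit log IgG on group, randomisation stratum, site and log maternal IgG to the same antigen. Report the GMC ratio with 95% CI as the one main GMC analysis, with the t test at most supportive.
- **(b) Effect modification, same antigens:** fit group, stratum, site and group × stratum, without maternal IgG. Report the GMC ratio with 95% CI in each stratum and the interaction estimate with its CI, as estimation rather than a pass-or-fail test. Add group × log maternal IgG as a supportive analysis.
- **(c) Hypothesis 3 and objective 1:** keep the maternal dTpa comparison unadjusted for maternal IgG, using confirmed status as section 5.3 describes. State on which side infants of mothers with infection only are counted.
- **(d) Other antigens:** use the randomisation stratum in place of dTpa status; no maternal covariate is available.

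The cost is analysis wording. The stratum and the maternal pertussis assay are already planned, so no sample, visit or infant is added.
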